## Abstract

**Background:**

Optimal anticoagulation using vitamin K antagonists prevents strokes associated with atrial fibrillation and heart valve replacements. Preparedness for self-monitoring and self-management could improve outcomes, but this remains a challenge.

**Objective:**

This study aimed to outline the methodology for developing and validating the PERSONAE scale, a self-report measure designed to assess the preparedness for self-monitoring and self-management of oral anticoagulation in adult patients.

**Methods:**

This study comprises 2 main phases, and it adheres to the “COnsensus-based Standards for the selection of health Measurement INstruments” (COSMIN) guidelines for instrument development. The first phase involved the conceptualization of the PERSONAE scale, where a comprehensive literature review and a consensus meeting among experts were conducted to draft the initial items. Face and content validity were then established through an expert panel review. In the second phase (ongoing), a detailed sampling methodology will be used, targeting adult Italian patients on long-term oral anticoagulation. According to a performed simulation-based power analysis, the study aims to recruit a sample size of approximately 500 participants by using a combination of convenience and snowball sampling. Data collection will be facilitated through web-based surveys distributed through social media and patient networks, ensuring a wide and representative sample. Analytical procedures will include Mokken scaling analysis for item selection and confirmatory factor analysis to validate the scale’s structure. In addition, internal consistency will be assessed using Molenaar Sijtsma statistics.

**Results:**

The scale’s content derived from phase 1 (process completed in December 2023) is grounded in a comprehensive literature review and based on the assessments of a panel of 12 health care expert professionals. The PERSONAE scale derived from phase 1 encompasses 20 items reflecting essential behaviors needed to assess the preparedness for self-monitoring and self-management of oral anticoagulation. Each item obtained a content validity ratio higher than 0.67, which is the critical content validity ratio indicating the minimum level of agreement among the experts for an item to be considered essential beyond the level of chance at a significance level of .05 for a 1-tailed test. From January 2024 to May 2024, we conducted the initial round of data collection and use Mokken scaling analysis to select items. A second round of data collection for confirmatory factor analysis was scheduled from June 2024 to September 2024, which will validate the scale’s unidimensional structure. We expect to achieve robust psychometric properties, including high internal consistency and validated constructs.

**Conclusions:**

The PERSONAE scale will be a valuable tool to assess patients’ preparedness for self-monitoring and self-management of oral anticoagulation. The study’s insights into technology-assisted learning preferences will inform the design of future educational interventions to enhance preparedness in adult patients.

**Trial Registration:**

ClinicalTrials.gov NCT05973240; https://clinicaltrials.gov/study/NCT05973240

**International Registered Report Identifier (IRRID):**

PRR1-10.2196/51502

## Introduction

Vitamin K antagonists (VKAs), such as warfarin, are a group of medicines used to thin the blood, preventing the formation of harmful blood clots that can lead to stroke [1]. They function by inhibiting Vitamin K-dependent coagulation factors, which are essential for blood clotting. This class of medications is particularly vital for reducing the risk of stroke associated with atrial fibrillation and heart valve replacements, especially when direct oral anticoagulants are unsuitable for certain individuals, such as adults with multiple morbidities [1]. The use of oral anticoagulants globally is on the rise, reflecting an increasing need to manage conditions predisposing individuals to increased thromboembolic risks. Currently, about 2 out of every 100 Italians are on oral anticoagulants [2], including both direct and indirect agents [3]. This increasing prevalence underscores the necessity for regular monitoring of prothrombin time and appropriate dose adjustments, as inadequate monitoring and dose management could lead to serious adverse reactions and complications. Several studies have highlighted the risks associated with insufficient monitoring in the last 2 decades [4,5]. For instance, it was highlighted that patients on warfarin who did not have their prothrombin time regularly monitored were at a higher risk of major bleeding complications [4]. A meta-analysis published in 2020 confirmed that with the rising number of patients on oral anticoagulants, there is a proportional increase in adverse events related to inadequate monitoring [5].

People on long-term oral anticoagulation can use point-of-care testing equipment (POCT) to monitor their blood clotting time, typically measured by the international normalized ratio (INR) [6]. In managing their anticoagulant medication, these individuals have 2 primary options: self-management, where they adjust their medication dosage based on a predetermined dose-INR schedule, allowing them greater autonomy and immediate response to INR readings, or self-monitoring, where they measure their INR levels independently but consult health care providers to make dosage adjustments [7]. This distinction is crucial as self-management empowers patients to take full control of their therapy, potentially improving their adherence and outcomes, while self-monitoring still relies on professional guidance for dose adjustments [8,9].

Numerous studies and systematic reviews have demonstrated that these self-testing approaches are equally effective, if not superior, to routine physician-managed anticoagulation monitoring, providing evidence that patient-led monitoring can enhance therapy management and patient satisfaction [8,9]. For instance, a systematic review reported that patients who self-managed their oral anticoagulation therapy had significantly better control over their INR levels and fewer thromboembolic events than those who relied on professional monitoring [10]. In this context, a solid randomized controlled trial found that self-management was associated with higher patient satisfaction and better quality of life due to increased control over their health [11]. However, the choice between self-management, self-monitoring, and physician-managed care should be individualized based on patient characteristics. Recent researches highlight that health-related quality of life in anticoagulated patients varies significantly, indicating how some patients may benefit more from self-management while others may find self-monitoring or physician-managed care more suitable [9,12,13]. In addition, the quality of anticoagulation control, traditionally assessed by the time in the therapeutic range (%TTR), is enhanced by using recommended coagulometers like CoaguChek XS, which are globally endorsed, particularly in response to the COVID-19 pandemic [14,15].

While self-monitoring and self-management approaches have garnered strong evidence for their effectiveness and cost-effectiveness, a Cochrane review highlighted the need for further research into factors influencing individuals’ preparedness for self-testing [8]. These factors include both psychological preparedness and preparedness in terms of objective equipment. Psychological preparedness encompasses patients’ self-management knowledge, motivations for medical attention, health literacy, self-efficacy, and perceived and actual support systems [13,16]. Specifically, patients’ knowledge about self-management affects their ability to understand and manage their treatment, while motivations for seeking medical attention could influence their commitment to regular monitoring. Health literacy impacts their ability to comprehend medical instructions and make informed decisions, and self-efficacy relates to their confidence in performing self-testing tasks [17]. Finally, perceived and actual support systems are crucial in providing the necessary resources and emotional support for effective self-management. Preparedness in terms of objective equipment involves access to and familiarity with POCT devices and other necessary tools. Evaluating preparedness for self-management and self-monitoring is therefore crucial in tailoring health care delivery, enhancing efficiency, and adequately preparing patients for self-testing [18]. The interaction between psychological preparedness and preparedness regarding objective equipment is critical. Patients who are psychologically ready but lack the necessary equipment, or vice versa, may not effectively self-manage their condition. Therefore, both aspects must be addressed to ensure successful self-management and self-monitoring.

In Italy, for instance, adopting self-testing is complicated by organizational and professional barriers, such as the cost of POCT devices and concerns regarding the loss of direct control over treatment management [12]. Addressing this gap is essential, as enhancing patient preparedness through targeted interventions could substantially improve the effectiveness and patient outcomes of self-management programs, ultimately transforming anticoagulation therapy practices globally. The PERSONAE scale specifically addresses these gaps by assessing domains of preparedness and providing its comprehensive measure for self-management and self-monitoring. Thus far, no measures of the preparedness for self-monitoring and self-management exist in relation to this population. Therefore, the aim of this protocol is to outline the methodological steps for the development and validation of the PERSONAE scale, a self-report measure intended to assess the preparedness for self-monitoring and self-management of oral anticoagulation in adult patients. The study is currently focused on the Italian adult patient population, carefully considering the scalability and adaptability of the PERSONAE scale for diverse age groups and international settings. In addition, it aims to pinpoint the most favored technology-assisted learning options among patients undergoing anticoagulation therapy. The PERSONAE scale is expected to improve existing self-management protocols and practices by identifying areas where patients may need additional support or resources after a detailed assessment of patient preparedness. The findings from this pioneering research will lay the groundwork for innovative technology-assisted educational programs designed specifically to boost preparedness for self-monitoring and self-management of oral anticoagulation, marking a significant advancement in patient-centered health care solutions.

## Methods

### Study Design

This methodological, multiphase study comprises 2 main phases to develop and validate the PERSONAE scale for assessing the preparedness for self-monitoring and self-management of oral anticoagulation in adult patients. The protocol adheres to the “COnsensus-based Standards for the selection of health Measurement INstruments” (COSMIN) guidelines for instrument development [19].

Phase 1 focused on conceptualizing the PERSONAE scale through a developmental methodological approach involving 3 primary steps. First, a literature review was conducted to identify all relevant elements related to the preparedness for self-monitoring and self-management of oral anticoagulation (anticipated between May 2023 and July 2023). This review was recently published elsewhere [13]. Second, a consensus meeting among developers was held to examine the findings of the literature review and endorse its synthesis (anticipated time: September 2023). Finally, the situations representing patients’ preparedness will be operationalized, and an external panel of experts, including nurses, physicians, and pharmacists, will determine the face and content validity of the newly developed scale (anticipated time: October 2023). Phase 2 focused on the validation procedures. Initially, the PERSONAE scale, containing items with acceptable content validity, was used for cross-sectional data collection from January to May 2024. The Mokken scaling analysis (MSA) procedure will be used to assess how the items in the first version of the scale behave in response to varying levels of the theoretical latent trait (preparedness). MSA is preferred over exploratory factor analysis in this study as it allows selecting items with the highest scalability, leading to a brief, unidimensional measure computed in a single score. Once a stable unidimensional PERSONAE scale is developed, a second round of cross-sectional data collection was performed from June to September 2024 to cross-validate the plausible unidimensional structure of the scale.

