### Sample Size

The sample size for phase 1 will be 8-12 experts. The sample size required for phase 2 to perform the Mokken scaling analysis was determined considering the 20 items derived from phase 1 (content validity phase). A simulation-based power analysis was performed in R (R Foundation for Statistical Computing; library “Mokken”), as shown in Multimedia Appendix 1. The aim of the simulation was to estimate a sample size that would provide sufficient statistical power, set at 0.8, to detect a minimum H coefficient of 0.3, indicative of a moderate scale according to Mokken’s hierarchy. The H coefficient in Mokken scaling analysis measures the strength of the hierarchical relationship among items in a scale as it quantifies the extent to which items form a cumulative scale. A custom simulation function was created using R statistical software, with the following parameters defined: 20 items, initial sample (n= 200), number of simulations=100, desired power=80%, minimum H coefficient=0.3, and maximum number of iterations=30. For each simulation iteration, the function generated a matrix of binary data representing responses to the 20 items, with responses simulated under a simple random model (ie, the probability of success was 0.5 for each item). The results from the simulation suggested that a sample size of 500 patients would be needed to achieve the desired power of 0.8 for our MSA. The MSA procedure will help reduce the number of items to the first 10-15 items that define the preparedness for self-monitoring and self-management of oral anticoagulation in adult patients. The required sample size for the second round of data collection will be determined through Monte Carlo simulations, aiming to achieve a power of 0.8 for the confirmatory factor analysis (CFA) model.

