### Data Analysis

The data analysis will involve the use of various statistical methods to develop and validate the PERSONAE scale.

For the first data collection round, MSA will be conducted using the “mokken” package in R [23]. MSA allows for the hierarchical evaluation of items, and the most relevant items that measure preparedness for self-monitoring and self-management of oral anticoagulation will be selected for the PERSONAE scale [24]. Loevinger’s coefficient of homogeneity function will be used to assess the scalability of the items. Monotonicity violations will be checked, and violations below 80 will be consistent with the requirements of a Mokken scale [23,25]. Loevinger’s coefficients of homogeneity (H) at the scale, item, and pairs of items level will be computed, where H values equal to or greater than 0.3, 0.4, or 0.5 indicate weak, moderate, or strong scales, respectively [23,25]. Item pairs violating monotonicity will be excluded, and floor and ceiling effects in data distribution will be assessed. Invariant item ordering (IIO) will be performed to further narrow down the pool of questions based on monotone homogeneity [25]. The IIO procedure will remove items one at a time until no significant violations are found. The Htrans (H^T^) coefficient will express the accuracy of the IIO selection, and H^T^>0.3 will denote proper IIO process and consistent Mokken scales. The final set of questions will be used to calculate ρ coefficients for reliability using the Molenaar-Sijtsma technique [26]. This approach is particularly adequate for assessing reliability in MSA because it provides a robust estimate of the internal consistency for nonparametric scales. The Molenaar-Sijtsma technique is well-suited for evaluating the scalability and reliability of the items within the scale, ensuring that the PERSONAE scale reliably measures the construct of preparedness for self-monitoring and self-management of oral anticoagulation.

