CFA will be used to cross-validate the plausible unidimensional structure of the PERSONAE scale derived from the MSA, theoretically containing 10-15 items, using Mplus 8.1 (Muthén and Muthén, 2017). An unrestricted and unspecified model will be used with a maximum likelihood robust estimation of parameters. A confirmatory factor analysis with covariates will be used to estimate measurement invariance between subgroups if linear relationships between participant characteristics and the scale’s total score are detected [27]. Modification indices will be explored to identify items causing a violation of invariance. Items causing invariance will be evaluated for possible deletion from the final scale. The adequacy of confirmatory factor analyses in explaining sample statistics will be assessed using various fit indices, such as chi-square, chi-square/degree of freedom, comparative fit index, Tucker-Lewis index, and root mean square error of approximation [28]. Invariance testing based on different levels of CCI and other potential confounders will be considered if needed and is feasible to ensure that the scale functions equivalently across groups with varying levels of comorbidity and demographics.

Missing data will be managed using an available-case approach for missingness lower than 5% or regression imputations for missingness equal to or higher than 5%, assuming missing at random. The significance level for all analyses will be set at 5%. The software used for the analysis will include Mplus (version 8.1, Muthén and Muthén), IBM SPSS Statistics for Microsoft Windows version 27, and R (version 4.2.1, R Foundation for Statistical Computing).

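### The reason given for Mokken scaling over exploratory factor analysis does not hold as written: the stated round-1 rules do not test dimensionality, and two correlated dimensions can pass as one scale

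*Protocol article*

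**What the plan says.** Study Design in the protocol article chooses Mokken scaling over exploratory factor analysis on the ground that "it allows selecting items with the highest scalability, leading to a brief, unidimensional measure computed in a single score". It moves to the second data collection "Once a stable unidimensional PERSONAE scale is developed", so unidimensionality is treated as settled by the end of round 1.

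Data Analysis then lists the round-1 rules:

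- H is computed for the scale, the items and the item pairs, and "H values equal to or greater than 0.3, 0.4, or 0.5 indicate weak, moderate, or strong scales, respectively".
- For monotonicity, "violations below 80 will be consistent with the requirements of a Mokken scale".
- For item ordering, "The IIO procedure will remove items one at a time until no significant violations are found", with an H^T above 0.3 accepted.
- Reliability is the Molenaar-Sijtsma rho on the items that remain.

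The first structural test named comes in the second sample: "CFA will be used to cross-validate the plausible unidimensional structure of the PERSONAE scale derived from the MSA". The Introduction says of the factors that influence readiness for self-testing: "These factors include both psychological preparedness and preparedness in terms of objective equipment". It adds that a patient may have one and lack the other, and later speaks of preparedness as having domains.

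**The concern.** Item H is in effect an average of an item's association with all the other items. The monotonicity check relates each item to the rest score over all the other items. If the items measure two traits that are moderately correlated, each item still rises with the rest score and its average association can still exceed 0.3. Item ordering concerns relative difficulty, and rho concerns reliability. A set that meets all these rules is therefore scalable but need not be unidimensional, so the stated reason for setting exploratory factor analysis aside does not follow.

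At stake is the single score, which is the study's main product. If two dimensions pass round 1 together, the score adds two traits. The round-2 sample is then spent testing a structure that the round-1 data could already have called into question.

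**Working it through.** **Inputs from the documents.** 20 items (Sample Size), a 5-point response scale (Results), about 500 respondents in round 1 (Sample Size), and the round-1 rules above.

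**The plan's own figure.** The only related figure is n=500, from a simulation of binary items with success probability 0.5. Read as independent items, that model gives H near 0 (largest value 0.012 at n=500) and never reaches 0.3 at any n from 200 to 5000. The 500 could not be reproduced from it. That is a separate matter, and n=500 is taken as given here.

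**Assumed, not in the documents.** Two factors of 10 items each, loadings 0.7 or 0.8, factor correlation φ from 0 to 0.7 (φ≈1 as the one-dimensional control), two spreads of item difficulty, 20 samples per cell. The monotonicity and item-ordering checks were coded from the usual rules, not run in the R package.

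**Step 1: why H passes.** The 20 items form 190 pairs: 90 within a factor and 10×10=100 between factors. With Hw and Hb the typical pair H within and between factors, scale H is approximately

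(90·Hw + 100·Hb) / 190.

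- Loading 0.8, φ 0.5: (90×0.63 + 100×0.32)/190 = 0.47; simulated 0.46 to 0.47.
- Loading 0.7, φ 0.5: (90×0.49 + 100×0.25)/190 = 0.36; simulated 0.36.
- Loading 0.7, φ 0.7: (90×0.48 + 100×0.33)/190 = 0.40; simulated 0.40 to 0.41.

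With Hw=0.49, scale H reaches 0.30 once Hb is (57 − 44.1)/100 = 0.13. Between-factor pairs can thus lie far below 0.3 while the scale passes.

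**Step 2: the H, item-H, monotonicity and item-ordering rules together.** Ranges cover the two difficulty spreads.

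| Loading | φ | Scale H | Label | Passes, both dimensions kept | At least one pair H below 0.3 | Automated selection at 0.30 keeps one scale |
|---|---|---|---|---|---|---|
| 0.7 | 0.5 | 0.36 | weak | 55–85% | 100% | 20% |
| 0.7 | 0.6 | 0.37–0.38 | weak | 75–90% | 100% | 65–95% |
| 0.7 | 0.7 | 0.40–0.41 | moderate | 85–100% | 100% | 100% |
| 0.8 | 0.5 | 0.46–0.47 | moderate | 55–95% | 95–100% | 90–95% |
| 0.8 | 0.6 | 0.50–0.51 | strong | 75–95% | 70% | 100% |
| 0.8 | 0.7 | 0.52–0.54 | strong | 80–100% | 5–10% | 100% |

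With 20 samples, the standard error of a 55% rate is √(0.55×0.45/20) = 0.11, so these rates are approximate.

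**Step 3: where the rules do stop it.** At φ=0, 0% passed at either loading. At loading 0.7, 0% passed at φ=0.2 and 0–5% at φ=0.3. At loading 0.8, 35–45% passed at φ=0.2 and 70% at φ=0.3. At loading 0.65, judged on item H alone, all 20 items reached 0.3 in 3–8% of samples at φ=0.5 and 70–78% at φ=0.7 (separate simulation runs).

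**Step 4: what a dimensionality check shows on the same data.** Parallel analysis found two factors in every two-factor sample with φ up to 0.7 and in none of the one-dimensional controls. In a separate simulation at loading 0.75, automated item selection with the lower bound raised to 0.45 separated the factors in 97–100% of samples; at 0.30 it did so in only 0–30%.

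**Step 5: what round 2 would see.** A one-factor fit in a fresh sample of 500 at loading 0.8 gave RMSEA about 0.14 and CFI 0.70–0.78 at φ=0.5, and RMSEA 0.11 and CFI 0.83 at φ=0.7. Sample Size foresees 10 to 15 items. At loading 0.75, trimming to 15 by lowest item H kept at least three items of each factor, and the fit stayed poor (RMSEA 0.09–0.11, CFI 0.82–0.90). Trimming to 12 usually left about ten items of one factor and at most two of the other; the fit then looked acceptable (RMSEA about 0.05–0.08, CFI 0.94–0.97).

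**The case against.** The case on the other side has real force in five places.

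- **The structure is assumed.** A reader might infer that the protocol itself expects a two-dimensional item set. The documents do not support that. The Introduction describes factors that influence preparedness, not subscales; all 20 items share one question stem; and the items are in an appendix that is not shown.
- **Acceptance is not universal.** A reader might infer that any clearly two-dimensional set passes as a moderate scale. Uncorrelated factors, the clearest case, never passed, and item-ordering removal often stripped out one dimension when the correlation was low. The label is not fixed either: the same results run from weak to strong, and Sample Size calls H=0.3 "indicative of a moderate scale" where Data Analysis calls it weak.
- **Pair-level H is computed.** A bound of 0.3 on every pair would flag most of these sets, with loadings of 0.8 and φ=0.7 the main exception. Data Analysis does not state that bound as a rule, but weak between-factor pairs would be visible to someone who looked.
- **Round 2 is an independent test** of a structure that Data Analysis calls only plausible. It may detect the misfit. A reader might infer that no data would then be left to develop the right structure; that is wrong, because the round-1 data on all 20 items remain. What is missing is a planned further sample to confirm a revised structure.
- **This is a condensed article.** Automated item selection is a usual part of Mokken scaling and may be in the full protocol, so its absence here is no finding. At a single bound of 0.30, however, it would often not separate correlated dimensions.

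What survives is narrower. A reason stated in the article for a design choice is not valid as written, and following the stated rules can carry two correlated dimensions forward as one score.

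**Conclusion.** The point holds in limited form and should be fixed. The stated round-1 rules do not test dimensionality, so selection on scalability does not by itself produce a unidimensional measure. The 55% to 100% acceptance rate rests on assumed loadings of 0.7 to 0.8, factor correlations of 0.5 to 0.7, an even 10+10 split and n=500, and on reading pair-level H as reported but not used for exclusion. More than one dimension is realistic from the Introduction but is not shown to exist in these items. The round-2 CFA is a partial safeguard: it can detect the problem, but its detection depends on which items survive the trimming.

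**What to change.** 1. On the round-1 data, before any item is dropped, run automated item selection on all 20 items with the lower bound raised from about 0.30 to 0.55 in steps of 0.05. Add a parallel analysis, and inspect pair-level H between any clusters that appear.
2. Claim one scale only if these agree. Otherwise take a prespecified comparison of a one-factor with a two-factor (or bifactor) model to round 2.
3. Reword the Study Design sentence: Mokken scaling selects scalable items, and unidimensionality is checked separately.

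No new participants are needed. The cost is a few lines of code on round-1 data and a short change of text. The downside is that the analysis may show that a single total score is not justified.
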